### Participants

Community-dwelling adults with a confirmed diagnosis of PD (by neurologist report) will be recruited. Inclusion criteria are (a) aged over 18 years; (b) able to communicate in English; (c) able to provide informed consent; (d) living in the community, (e) availability of and experience using computer or tablet technology with internet access and (f) willing to receive intervention in their homes. Exclusion criteria are (a) pre-morbid or current major psychiatric or other neurological disorder; (b) diagnosis of dementia or severe cognitive impairment indicated by a score of less than 13 on the cognitive screening assessment; (c) significant sensory impairment (visual or hearing) which prevents involvement in the intervention and/or reliable completion of outcome measures; (d) communication disorder (severe expressive and/or receptive aphasia) which prevents involvement in the intervention and/or reliable completion of outcome measures; (e) complete dependence on others for personal care; and (f) receiving concurrent allied health or cognitive intervention working on the same goals.

### Procedures

The study will be advertised online on the Parkinson's Queensland Research Participation Opportunities page, on their social media platforms and via the member's newsletter. Potential participants will self-select and contact the interventionist if they are interested in participating in this research. During first contact via telephone, the interventionist will undertake eligibility and cognitive screening, provide participants with information about the study, and obtain verbal consent to participate. Potential participants will be emailed a copy of the participant information and consent form to aid their decision-making process with regards to study participation. Study participation will be offered if eligible and score above the cut-off for the telephone Montreal Cognitive Assessment (T-MoCA). Participants will be emailed the link to the online survey once the offer of participation is verbally accepted. The online questionnaire collects demographic and disease information and self-report outcome measures and will be completed independently by participants, outside session times. The interventionist will then complete a home visit to complete baseline assessments and program goal setting facilitated by the Canadian Occupational Performance Measure (COPM) will occur. Hard copies of the participant information and consent forms will be provided to participants during the first home visit, and written consent obtained. Using the prioritized goals identified during the COPM interview, Goal Attainment Scales (GASs) for each goal will be created to enable objective measurement by an independent assessor, according to the procedure used previously for the combined use of the COPM and GAS (Doig et al., 2010). Baseline performance in goal activities will be recorded objectively to enable independent ratings of goal performance by a masked assessor. Following this visit, participants will be randomly assigned to either the CO-OP-I or a WLC with a blocked equal allocation, stratified by scores on the Addenbrooke's Cognitive Evaluation – III (ACE-III), by a computer-generated randomization schedule. A summary of the timeframes for consent, screening, goal setting, randomization, and outcome measurement across the phases of the study are outlined in Table 1.

**Table 1 table1-00084174231156287:** Phases of Study

	Enrolment	Baseline	Intervention		Follow-up
Timepoint		*T1: prior to intervention*	*T2: 10 weeks*	*T3: (20–22 weeks)*	*T4: (30–32 weeks)*
Enrolment					
Eligibility; T-MoCA	✓				
Informed consent	✓				
Goal setting conducted using COPM and GASs established		✓			
Random allocation		✓			
Assessments:					
Age; sex; education level; work status; disease duration; medication; ACE-III; NART; H&Y		✓			
Primary outcomes: COPM; GAS; PQD		✓ Both groups—baseline measurement	✓ Post-WLC/ pre CO-OP-S ✓ Post-CO-OP-I	✓ Post-CO-OP-S ✓ CO-OP-I 3-month follow-up	✓ CO-OP-S 3-month follow-up
Functional outcomes: HADS; AS; PDQ-8; FSS; GSE; DLSES; NEADL;S&E		✓ Both groups—baseline measurement	✓ Post-WLC/ pre CO-OP-S ✓ Post-CO-OP-I	✓ Post-CO-OP-S ✓ CO-OP-I 3-month follow-up	✓ CO-OP-S 3-month follow-up

Abbreviations: AS = Apathy Scale; ACE-III is Addenbrooke's Cognitive Evaluation – III; COPM = Canadian Occupational Performance Measure; CO-OP-S = CO-OP standard intervention; CO-OP-I = CO-OP intensive intervention, DLSES = Daily Living Self-Efficacy Scale; FSS = Fatigue Severity Scale; GAS = Goal Attainment Scale; GSE = General Self-Efficacy Scale; HADS = Hospital Anxiety and Depression Scale; H&Y = Hoehn and Yahr Scale; NART = National Adult Reading Test; NEADL = Nottingham Extended Activities of Daily Living Scale; PDQ = Perceived Deficits Questionnaire; PDQ-8 is Parkinson's Disease Questionnaire – Short Form; S&E is the Schwab and England Activities of Daily Living Scale; T-MoCA = Telephone Montreal Cognitive Assessment; WLC = waitlist control.

Participants in the treatment group will commence treatment sessions for a 10-week period, following the intensive intervention protocol (CO-OP-I). Participants allocated to WLC will have a 10-week non-intervention period, before commencing the standard 10-week intervention protocol (CO-OP-S). Participants in the WLC will be reassessed post-WLC/prior to commencing CO-OP-S. A post-intervention assessment will be conducted immediately following the intervention and at 3 months post-intervention. Goal performance will be captured objectively using written logs and/or video-recorded performance, and subjectively on the COPM. Immediately following the intervention, a semi-structured qualitative interview will be conducted by the interventionist, who is an experienced occupational therapist specializing in neurological rehabilitation. Interviews will be audio-recorded with each participant to explore the participants’ experiences and perceptions about the CO-OP treatment approach. Audio recordings will be transcribed verbatim by an independent person and member checking will occur following theming to enhance the trustworthiness of results (Trainor & Graue, 2014). Additional information captured in the interventionist field notes and independent clinical observations about participant's experience of the CO-OP training will also be drawn upon to explore the semi-structured interviews and inform aspects of the feasibility study.

### Measures

Measures were selected in line with the International Parkinson and Movement Disorder Society (MDS) Task Force critique and recommendations in the literature regarding scales for use with people with PD. As per the MDS Task Force protocol, a scale is “Recommended” if it has (1) been applied to PD populations; (2) there are data on its use in studies beyond the group that developed the scale; and (3) if it was studied clinometrically and found to be valid, reliable, and sensitive to change (Schrag, 2012).

#### Screening Assessment

The Telephone-Montreal Cognitive Assessment (T-MoCA) (Pendlebury et al., 2013) will be used to screen cognition via the telephone prior to patient enrolment in the trial. Benge and Kiselica (2020) found that the T-MoCA was well tolerated by people with PD and was brief and easy to administer in their study validating the use of the T-MoCA in PD. Potential participants who score less than 13 on the T-MoCA will be excluded from the study as per recommendations in Benge and Kiselica (2020).

#### Demographic and Disease Data

Demographic and disease data collected at baseline via an online Qualtrics survey includes age, sex, education level, work status, disease duration, and medical management (i.e., levodopa dosage). Data collected in person during the initial home visit will include pre-morbid IQ, neuropsychological status, and disease severity.

The National Adult Reading Test (NART) (Nelson & Willison, 1991) is a 50-word reading test that provides reliable and valid estimates of IQ and has been shown to be relatively insensitive to the effects of various neurological conditions, including PD (Mathias et al., 2007). The NART will be used in this study to estimate the premorbid intelligence levels of participants to describe the study sample.

The ACE-III (Mioshi et al., 2006) is a brief cognitive screening battery assessing five neuropsychological domains (orientation and attention, memory, verbal fluency, language, and visuospatial function). The ACE-III score will be used to stratify participants for randomization. The stratification groups are no cognitive impairment and MCI. The cut-off score for this assessment will be 88 whereby a score of 100–89 is considered no cognitive impairment and a score of 88–77 is considered MCI (Senda et al., 2020).

The Modified Hoehn and Yahr (H&Y) scale (Hoehn & Yahr, 2011) is a 7-point Likert scale that focuses on the clinical impression of overall PD severity based on key aspects of disability and features of objective impairment. The H&Y scale will be used to measure disease severity/stage.

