## Random Allocation

Participants will be randomly assigned to either the CO-OP-I or a WLC group using blocked allocation, stratified by scores on the ACE-III. An independent senior member of the research team will create a computer-generated randomization schedule with concealment then allocate participants in chronological order from time of written consent.

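### The two ACE-III randomisation bands stop at 77, but eligibility sets no ACE-III floor, so an eligible participant scoring 76 or less is outside both printed bands

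*Protocol article*

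**What the plan says.** Under Demographic and Disease Data, the protocol article makes the ACE-III the stratification variable: "The ACE-III score will be used to stratify participants for randomization". It names two groups, "The stratification groups are no cognitive impairment and MCI", and sets one dividing value: "The cut-off score for this assessment will be 88". The same sentence then bounds each group: "a score of 100–89 is considered no cognitive impairment and a score of 88–77 is considered MCI". Random Allocation repeats the method, "using blocked allocation, stratified by scores on the ACE-III", and has an independent senior team member prepare a concealed schedule and allocate in order of written consent. Design and Setting gives a block size of 6.

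Eligibility rests on a different instrument. Under Participants, the cognitive exclusion is "diagnosis of dementia or severe cognitive impairment indicated by a score of less than 13 on the cognitive screening assessment". Screening Assessment identifies that instrument: "Potential participants who score less than 13 on the T-MoCA will be excluded from the study". Procedures makes the offer of participation by telephone once the person is eligible and passes the T-MoCA. The ACE-III is done in person at the first home visit, and random allocation follows that visit.

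**The concern.** A stratified schedule needs a rule that places every eligible person in exactly one stratum. Here the stratum bands and the eligibility rules come from different scales, and nothing in the article ties them together. The lower stratum is labelled mild cognitive impairment and closed at 77, while the exclusion criterion removes only diagnosed dementia or severe impairment on the telephone screen. Impairment between mild and severe, as the article measures each, is neither excluded nor given a band.

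The mismatch comes to light late. When the ACE-III score is known, the person has accepted the offer and is at the visit where written consent and baseline assessments are completed. The person allocating must then either choose a stratum without a written rule or leave out someone who meets every stated criterion. The first is a small departure from a pre-specified allocation. The second changes who is in the trial by a rule that is not among the eligibility criteria.

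**Working it through.** The plan states no figure to reproduce here. The check is whether the stratum bands cover every ACE-III score that the eligibility rules admit.

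1. **Scores given a band** (Demographic and Disease Data): 89 to 100 for no cognitive impairment and 77 to 88 for MCI. The bands meet at 88/89 without overlap. Together they cover 77 to 100.

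2. **Scores admitted** (Participants, Procedures, Screening Assessment): the cognitive exclusions are a diagnosis of dementia and a T-MoCA below 13. Neither refers to the ACE-III, so eligibility sets no lower ACE-III limit.

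3. **Difference:** every admissible score of 76 or less has no band. The article gives only the top of the scale, 100. If the scale starts at 0 (an assumption), the bands cover 100 − 77 + 1 = 24 of 101 integer scores and leave 76 − 0 + 1 = 77 without a band. This counts scale points, not people; most of those points may never occur in an eligible person.

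4. **Could the T-MoCA rule close the gap indirectly?** Only if passing the T-MoCA implied an ACE-III of 77 or more. The article does not relate the two scales, so this can be neither assumed nor ruled out.

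5. **Order of events** (Procedures, Table 1, Demographic and Disease Data): telephone T-MoCA and offer, then the home visit with written consent and ACE-III, then randomisation. The order of consent and ACE-III within the visit is not stated. Any problem with a low score therefore arises after the offer and before allocation.

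6. **Number affected:** this would be the number enrolled times the share scoring 76 or less. The article gives neither, so no count is offered.

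7. **Use in the analysis** (Data Analysis): the models are 2 × 2 (Treatment × Time) mixed ANOVAs, and covariates are chosen by baseline t-tests between groups. The ACE-III stratum is not named as a factor. Stratified allocation is designed to balance the groups on this variable, so a test for baseline imbalance will tend to leave it out, whether or not it predicts outcome.

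**The case against.** The strongest reply is that the operative rule is already exhaustive. The article specifies two groups and one cut-off, 88, and one cut-off with two groups sorts every score into 89 or more or 88 or less. On that reading the printed ranges are interpretive labels taken from a cited source, and a low scorer goes into the lower stratum. This is the natural reading and may be what was done. It does not fully answer the point, because the same sentence closes the lower band at 77 and the text nowhere says that lower scores belong there. The two halves of the sentence need to agree.

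A second reply is that a journal article leaves the stratum list to the full protocol. That would answer a silence. Here both bounds are printed, and they do not fit the article's own eligibility rules.

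A third reply is that the affected group may be nearly empty. It is narrowed by the dementia exclusion, the T-MoCA threshold, the requirement for informed consent, and the exclusion of people completely dependent for personal care. This stands: the article cannot show how large the group is.

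A reader might also infer more than the documents support:

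- **That the T-MoCA is the sole cognitive bar.** It is not, because a dementia diagnosis also excludes. It is only the sole cognitive score used for eligibility.
- **That the gap biases the treatment comparison.** Placing a low scorer in the lower stratum leaves allocation random and concealed. It only makes that stratum more heterogeneous.
- **That a stratum-adjusted analysis is left undefined.** None is planned.
- **That low scorers are the group in which the trial's question matters most.** No analysis by cognitive level is specified.

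**Conclusion.** The concern holds as a mismatch between two stated rules. The lower randomisation band ends at ACE-III 77, eligibility sets no ACE-III floor, and an eligible person scoring 76 or less is outside both printed bands. This follows from the text and needs no assumption.

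The practical size is modest and unknown. The number of such people cannot be derived from the article and may be zero. What is at risk is an ad hoc stratum placement, or the loss of an eligible person after baseline. The article does not say that anyone would be dropped, and any such loss would precede randomisation. This is a correction worth making because it is definite and nearly free; it does not threaten the validity of the trial.

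**What to change.** 1. Define the strata exhaustively under Demographic and Disease Data: ACE-III 89 or more versus 88 or less. This keeps the stated cut-off and changes no eligibility rule. If the investigators did intend a lower ACE-III limit for entry, the eligibility section and the bands must be reconciled; that choice is theirs. Cost: one sentence, and a check that the randomisation schedule matches it.

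2. The Abstract shows that the trial had started before registration. For anyone already randomised with a score below 77, record the stratum actually used and report it. Cost: a file note.

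3. Under Data Analysis, include the two-level stratum in the models from the outset instead of leaving it to the baseline t-tests. Enter it with its interaction with time; with two time points, a stratum main effect alone does not enter the Treatment × Time test. Cost: one degree of freedom. For the pre–post comparison with N participants, the error degrees of freedom for that test fall from N − 2 to N − 3.

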#### Primary Outcome Measures

COPM (Law et al., 2015) identifies occupational performance problems. Participants rate the importance of problems identified, which ensures the most important areas are prioritized and are the focus of program goals. Participants then rate their performance (objective) dimension and a satisfaction (subjective) dimension on a 10-point Likert scale (McColl et al., 2016). From the self-assessed scores, COPM performance scores and satisfaction scores can be calculated. Following the intervention, the client re-evaluates their self-rating for performance and satisfaction for the problems addressed. These scores are used to calculate the composite performance and satisfaction change scores for the COPM. A change of two points is considered clinically important (Law et al., 2015). The COPM will be used to identify and measure self-rated performance and satisfaction in participants chosen occupational performance goals.

GAS (Kiresuk & Sherman, 1968) is an outcome measure that uses a 5-point measurement scale (ranging from −2 to +2), with calculation of a *T* score possible. Expected outcomes are scored 0; baseline is −1 with scaling ranging to −2 to capture the potential for occupational performance deterioration and +1 and +2 for exceeding expected outcomes. The GAS will be used to objectively measure attainment of program goals when rated by a masked assessor.

Performance Quality Rating Scale (PQRS) (Martini et al., 2015) is an observational measure of performance quality rating participants’ performance of their goal activities using a 10-point Likert scale. A rating of “1” indicates that the skill is not done at all, and “10” indicates that the skill is performed very well (Martini et al., 2015). The criteria consider both the activity steps and the performance quality, with scoring based on descriptions of progressing skill level developed for every rating level (Miller et al., 2001). The PQRS will be rated by the intervention therapist.

Perceived Deficits Questionnaire (PDQ) (Sullivan et al., 1990) is a self-rated 20-item tool representing several domains of perceived cognitive functioning including attention, retrospective memory, prospective memory, and planning and organization. The PDQ will be used to measure perceived EF in this study.

The Nottingham Extended ADL (NEADL) (Nouri & Lincoln, 1987) consists of 22 items in four subscales (mobility, domestic, kitchen, and leisure). The items are rated using a 4-point Likert scale and items represent general ADL tasks, including IADLs, which have been shown to be most affected by executive dysfunction in PD (Cahn et al., 1998). The NEADL will be used to rate participants’ level of disability.

The Schwab and England ADL Scale (S&E) (Schwab et al., 1969) uses a percentile scale with 10% intervals, where 100% is “Completely independent… Unaware of difficulty” and 0% is “Vegetative functions…Bedridden.” The S&E will also be used to rate participant's disability levels.

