## Method

### Design and Setting

A parallel-group assessor-masked randomized controlled feasibility trial using blocked allocation (6 per block) to enable equal ratios between treatment and control groups. Intensive CO-OP (CO-OP-I) training will be compared to WLC to establish preliminary efficacy. Following a non-intervention period, the WLC will then undertake standard CO-OP (CO-OP-S) (Figure 1). A mixed-method approach will be used to assess feasibility in terms of acceptability, demand, implementation, practicality, adaptation, integration, expansion, and limited-efficacy testing (Bowen et al., 2009). The study was approved by the UQ Human Research Ethics Committee (HREC) — 2020/HE002650 on February 9, 2021.

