**Figure 1. fig1-00084174231156287:**
[figure not shown]
CONSORT style study flowchart.

This study conforms to the recommendations made by Biundo et al. (2017) for cognitive rehabilitation trials for people with PD where feasible. Recommendations include cognitive profiling, cognitive domains targeted, randomization methods, optimal delivery of neuro-rehabilitation approach, important outcome measure domains, and inclusion/exclusion criteria.

This study involves a person with PD as a consumer from the beginning of the research process to enhance the relevance and usefulness of the research to people with PD (Graham et al., 2018). The involvement of the consumer in this study was from the initial stages and discussions about roles was guided by the involvement matrix tool (Smits et al., 2020) which describes five roles: Listener, Co-thinker, Advisor, Partner, and Decision maker. Collaboratively agreed-upon roles for this project included Advisor and Co-thinker.

The intervention will take place in each participant's home environment in Brisbane, Australia. The first author, an experienced clinician with adult neurological populations trained in CO-OP approach (Polatajko et al., 2001) will collect the data and administer the intervention. The masked assessor is an experienced clinician who did not deliver the intervention and is masked to treatment condition and phase.

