## Masking

Baseline and post-intervention GAS goal performance will be objectively rated (using the logs and video-recorded performance data) by a qualified occupational therapist assessor who is masked to treatment condition and not involved in the delivery of the intervention. GASs and assessment criteria used to score each program goal will be established by the interventionist at baseline.

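### The PQRS, listed with the primary measures in the text but not in Table 1, is scored by the treating therapist although a masked assessor already rates the same goal activities

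*Protocol article*

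**What the plan says.** All references are to the Protocol article.

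- **Design and Setting** calls the study "A parallel-group assessor-masked randomized controlled feasibility trial". The clinician who runs the study "will collect the data and administer the intervention". A second clinician has the masked role: "The masked assessor is an experienced clinician who did not deliver the intervention and is masked to treatment condition and phase".
- **Primary Outcome Measures** presents the PQRS as an observational scale that rates "performance of their goal activities using a 10-point Likert scale", and then says "The PQRS will be rated by the intervention therapist". In the same section the GAS is to be rated by a masked assessor.
- **Masking** covers the GAS only: "Baseline and post-intervention GAS goal performance will be objectively rated (using the logs and video-recorded performance data", by an occupational therapist who does not deliver the intervention.
- **Procedures** describes the source material: "Goal performance will be captured objectively using written logs and/or video-recorded performance, and subjectively on the COPM". It also places randomisation after the baseline home visit.
- **Table 1** gives the primary outcomes as the COPM, the GAS and an entry printed as PQD. The PQRS appears neither in the table nor in its list of abbreviations.

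**The concern.** An observer's rating of performance quality is the kind of outcome that masking is meant to protect. Here the observer is the person whose therapy is being evaluated. By T2 that person has offered 20 sessions to each CO-OP-I participant and none to each waitlist participant, so masking is impossible. The article gives no reason for the choice, although a masked rater of the same activities is already in place.

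What is at stake is the comparison of CO-OP-I with the waitlist, which serves the first-named objective, preliminary efficacy. The article intends the results to prepare for larger trials, so an inflated PQRS effect could carry over into their planning. The label assessor-masked would also lead a reader to assume protection that this measure does not have.

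**Working it through.** The article states no sample size, significance level, PQRS standard deviation or expected effect, so there is no figure to reproduce. The check sets the sections side by side and follows the rater's error through the planned contrast.

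**1. Who rates, and what that person knows**

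| | PQRS | GAS |
|---|---|---|
| What is rated | Performance of goal activities | Performance of goal activities |
| Rater | Intervention therapist | Separate masked occupational therapist |
| Knows the arm at T2 | Yes: delivers CO-OP-I from T1 to T2 | No: masked to condition and phase |
| Material | Not stated | Logs and video |

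**2. Where the error enters**

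Data Analysis plans a 2 × 2 (Treatment × Time) mixed ANOVA for CO-OP-I against waitlist, pre and post. It does not name the PQRS. I assume that the PQRS belongs to the outcomes covered there and is scored at T1 and T2. I also assume that the T1 score is given at the baseline visit, before allocation.

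The interaction contrast is

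Δ = (mean of CO-OP-I at T2 − mean of CO-OP-I at T1) − (mean of WLC at T2 − mean of WLC at T1).

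Let b0 be the rater's average error at T1. It is the same in expectation in both arms, because allocation has not yet happened. Let bI and bW be the average errors at T2 in CO-OP-I and WLC. Then

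E(Δ) = true effect + (bI − b0) − (bW − b0) = true effect + (bI − bW).

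The baseline error cancels and the T2 difference does not. If the rater is masked, bI = bW in expectation. If the rater knows the arm, nothing in the design makes them equal. Each PQRS point of difference in leniency becomes one point of apparent effect. Baseline covariates and multiple imputation, the adjustments that Data Analysis mentions, do not identify bI − bW.

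**3. Direction and size**

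The rater scores the results of their own therapy, so bI > bW is the likelier direction. The documents contain nothing from which its size could be calculated.

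**4. Status of the PQRS**

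Six measures are described under the heading "Primary Outcome Measures": COPM, GAS, PQRS, PDQ, NEADL and S&E. In Table 1, COPM and GAS are in the primary row, with PQD there probably a misprint for PDQ. NEADL and S&E are in the functional row. The PQRS is in no row, so its primary status rests on the heading in the text alone, and Table 1 gives it no time points.

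**5. Whether masked scoring is possible**

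Procedures allows logs, video or both. Goals that were filmed can be scored by the masked assessor. For goals with only a written log, performance quality probably cannot be judged.

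**The case against.** The strongest reply has four parts.

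- **Primary status.** Table 1 leaves the PQRS out, so a reader who takes it as a settled primary outcome goes further than the documents allow. This stands. It makes the status a matter to reconcile, but it does not change who rates the scale.
- **Built-in protection.** The PQRS has written descriptions for each rating level, which limits the rater's freedom, and the masked GAS covers the same activities and can serve as a check. Both points stand as mitigation. Neither removes the rater's knowledge of the arm.
- **Feasibility trial.** Efficacy is only preliminary here, and the article openly confines masking to the GAS. That lowers the stakes, but preliminary efficacy is still the first objective.
- **Repairability.** No adjustment of the therapist's scores removes the bias, but stored video can be re-scored by a masked rater later. The loss is therefore not final where video exists.

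Three stronger readings are tempting and not supported:

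- **GAS coverage.** Because Masking speaks of baseline and post-intervention ratings, a reader might infer that the waitlist arm's T2 GAS and the follow-up GAS are rated by someone unmasked. No section says so. The GAS description sets no limit on time points, the assessor is masked to phase, and Table 1 schedules the GAS for both arms throughout. At most, one clarifying sentence is needed.
- **COPM.** A reader might infer that COPM re-ratings are given in front of the therapist. This follows only from the general statement about data collection. The COPM is in any case a self-rating by participants who know whether they have been treated, which is a different matter.
- **False-positive rates.** One could assume a standard deviation, an amount of over-rating and arm sizes, and calculate an inflated error rate. The result would only restate those assumptions.

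**Conclusion.** The point holds as a risk of detection bias, not as demonstrated bias. A measure described among the primary outcomes is an observational rating by the treating therapist, who knows the arm at T2, in a trial described as assessor-masked that already has a masked rater for the same activities. Any difference between arms in leniency adds directly to the CO-OP-I versus waitlist contrast, probably towards benefit. Its size is unknown.

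The conclusion about the rater rests on explicit statements in the article. Three things are assumed: that the PQRS enters the pre–post ANOVA, that its baseline score precedes allocation, and that a therapist's expectation favours their own treatment. The finding does not extend to the GAS or the COPM.

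**What to change.** 1. Have the existing masked assessor score the PQRS from video at every time point where video exists, in random order, with arm and time point hidden. Recordings should be checked for remarks that reveal either.
2. Where masked scoring is not possible, label the therapist-rated PQRS as unmasked and take it out of the primary set. Rest efficacy statements about observed goal performance on the masked GAS.
3. Reconcile Primary Outcome Measures with Table 1: state whether the PQRS is primary and when it is rated, and correct the PQD entry.
4. As a minor clarification, state in Masking that masked GAS rating covers T2 in both arms and the follow-up visits.

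**Cost.** Item 1 needs extra rating time from an assessor already in place, who must also be given the level descriptions for each goal. Goals recorded only in a written log cannot be scored this way unless they are also filmed, which would be an added procedure. Video is to be kept in the research data system, so sessions already filmed can be scored later. Items 2 to 4 are changes of wording.
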